## Introduction

Atrial fibrillation (AF) is the most common sustained cardiac arrhythmia. Over the last 20 years, the number of new cases of AF diagnosed each year has risen by 72%, and now surpasses the four most common causes of cancer combined.^1^ Moreover, it is estimated that up to 35% of the disease burden remains undiagnosed,^2^ and 15% of strokes occur in the context of undiagnosed AF.^3^

Oral anticoagulants can reduce the risk of stroke by up to two-thirds in those with AF at higher risk of stroke,^4^ and international guidelines recommend their use in patients with AF at elevated thromboembolic risk.^5^ Early detection of AF may permit the initiation of oral anticoagulation to reduce embolic stroke risk,^4^ and early antiarrhythmic therapy to reduce the risk of death and stroke.^6^ Accordingly, early AF detection is a key cardiovascular priority in the UK National Health Service (NHS) Long Term Plan,^7^ and the European Society of Cardiology recommends opportunistic screening by pulse palpation or ECG rhythm strip in persons aged ≥65 years and systematic ECG screening in those aged ≥75 years.^8^

Furthermore, AF frequently develops due to, and in parallel with, other cardiovascular, renal and metabolic conditions,^9^ and individuals with AF are at an increased risk of major cardiovascular events in excess of stroke including ischaemic heart disease, heart failure, chronic kidney disease, peripheral vascular disease and death.^10^ Thus, AF screening, with or without AF diagnosis, maybe a key opportunity for holistic management of cardiometabolic risk factors and unhealthy lifestyle behaviours to reduce an individual’s risk of later adverse events beyond that of stroke prophylaxis alone.

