## Methods and analysis

### Data sources and permissions

The derivation dataset will be the Clinical Practice Research Datalink-GOLD (CPRD-GOLD) dataset. This is an ongoing primary care database, established in 1987, which comprises anonymised medical records and prescribing data contributed by general practices using Vision software. It contains data for approximately 17.5 million patients, with 30% of contributing practices in England, and represents the UK population in terms of age, sex and ethnicity.^16^ In order to contribute to the database, general practices and other health centres must meet prespecified standards for research-quality data (‘up to standard’).^16 20^

Recorded information includes patients’ demography, clinical symptoms, signs, investigations, diagnoses, prescriptions, referrals, behavioural factors and test results entered by clinicians, and other practice staff. All clinical information is coded using Read Codes.^21^ Extracted patients will have patient-level data linked to Hospital Episode Statistics (HES), Admitted Patient Care (APC) and Office for National Statistics (ONS) Death Registration. The CPRD dataset has been used to develop or validate a range of risk prediction models.^22^

The extracted dataset, including linked data, comprises all patients for the period between 2 January 1998 and 30 November 2018 from the snapshot of CPRD-GOLD in October 2019. Over this study period, the CPRD-GOLD dataset comprises approximately 2 million patients eligible for data linkage at an up-to-standard practice, with over 200 000 patients having a record of AF during follow-up.

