To ascertain whether the prediction model is transportable to geographies outside of the UK, we will externally validate its performance in the Clalit Health Services (CHS) database in Israel. As a result of the National Health Insurance Law, Israeli citizens are required to enrol in one of four payer-provider health funds and receive free basic healthcare. CHS provides health insurance coverage to 4.8 million insured members and about two-thirds of the population aged >65 years. CHS is recognised globally as the primary source of evaluation of COVID-19 vaccinations and therapies.^23–26^ All clinical information is coded in International Classifications of Diseases, Ninth Revision (ICD-9). Receipt of vital status from the Ministry of the Interior ensures 100% follow-up of mortality. We will include participants insured by Clalit with continuous membership for at least 1 year before 1 January 2019: 2 159 663 patients with 4330 of them having a new incident of AF (AF and/or atrial flutter (AFl)) in the first half of 2019.

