### Prediction model outcome ascertainment

The outcome of interest is first diagnosed AF or AFl after baseline. Baseline is taken in the CPRD-GOLD dataset as the first entry of the patient into the dataset. We have included AFl as an outcome since it has similar clinical relevance, including thromboembolic risk and anticoagulation guidelines, as AF.^5^ These will be identified using Read codes in CPRD dataset. For HES APC events and underlying cause of death variables in the ONS Death Registration data file, ICD-10 codes will be used. For CHS, events will be identified using ICD-9 codes. It should be noted that a report has estimated that 305 262 individuals in the UK have undiagnosed AF,^27^ and so incidence of AF within the study may be underestimated as there will be individuals with unrecorded asymptomatic AF.

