**Figure 2 F2:**
[figure not shown]
A schematic representation of a multivariable logistic regression model or random forest model using data from electronic health records to provide risk prediction for incident AF. AF, atrial fibrillation.

Preprocessed patient-level data in CPRD-GOLD will be randomly split into an 80:20 ratio to create derivation and internal validation (or training and testing) samples. The split ratio is not a significant factor, given the volume of the sample size. The model parameters and drop-out rate will be chosen through a grid search and 10-fold cross-validation will be used (ie, 10% of the training data will be randomly selected as the cross-validation set). The multivariable logistic regression model will be developed with backward model selection with Akaike information criterion.^37^ The prediction window will be set at 6 months, as this is considered in keeping with the logistical time frames for organising AF investigation at scale.

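### Pooling 1998–2018 entries under a random split hides calendar drift from internal calibration, and the 2019 CHS cohort cannot separate country from era

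*Protocol article*

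**What the plan says.** All references are to the protocol article.

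- **Period.** Under Data sources and permissions, the CPRD-GOLD extract "comprises all patients for the period between 2 January 1998 and 30 November 2018 from the snapshot of CPRD-GOLD in October 2019".
- **Index date.** Under Prediction model outcome ascertainment: "Baseline is taken in the CPRD-GOLD dataset as the first entry of the patient into the dataset". Index dates can therefore fall anywhere in about 21 years.
- **Split and horizon.** Under Prediction model development, the patient-level data "will be randomly split into an 80:20 ratio to create derivation and internal validation (or training and testing) samples", and "The prediction window will be set at 6 months".
- **Internal checks.** Internal validation specifies AUROC, Brier score, a calibration plot, a calibration slope, net reclassification at the cohort's average 6-month incidence, and decision curves. The subgroups are age, sex and ethnicity. Calendar time is neither a subgroup nor among the candidate predictors listed under Predictor variables.
- **External check.** CHS members in Israel are indexed at 1 January 2019, with 4330 events among 2 159 663 patients in the first half of that year. The purpose given is to learn "whether the prediction model is transportable to geographies outside of the UK", and the Abstract calls it a geographical validation.
- **Trend.** The Introduction reports: "Over the last 20 years, the number of new cases of AF diagnosed each year has risen by 72" (per cent).
- **Updating.** Ethics and dissemination mentions updating only as a possibility once the model is in clinical use.

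**The concern.** The model is meant for screening current patients, so what matters for absolute risk is whether predictions fit recent entrants. A random split tests something else: whether they fit another random draw from the same 1998–2018 mixture. If the risk of a recorded AF diagnosis, given the predictors, changed over that time, errors of opposite sign in early and late entrants cancel in the pooled test set.

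CHS does not close the gap. It is later than every CPRD entry and also from another country and record system. Suppose observed risk in CHS exceeds predicted. The explanation could be that the model does not transfer to Israel, which bears on Aim 3, or that it is out of date, which would affect UK users equally. These call for different remedies, and the planned outputs do not distinguish them. Calibration, net reclassification at a fixed threshold and decision curves are exposed because they use absolute risk. Ranking and AUROC need not suffer.

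**Working it through.** **1. The plan's own figure.** No number is given for drift. The one computed design figure is the development sample size (200 parameters, Cox-Snell R² 0.01, shrinkage 0.95):

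n = 200 / [(0.95 − 1) × ln(1 − 0.01/0.95)] = 377 996.5, against 377 996 stated. It reproduces and is not in dispute.

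**2. What a random split can show.** Let w(t) be the share of entries at time t and r(t) the mean 6-month risk at t for a fixed predictor profile. A model without calendar time predicts about Σw(t)r(t). A random test set has the same w(t), so:

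- pooled test set: O/E = Σw(t)r(t) / Σw(t)r(t) = 1.00, whatever r(t) does;
- entrants at time t: O/E = r(t) / Σw(t)r(t), which the planned outputs do not show.

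A uniform shift in log-odds also moves the intercept rather than the slope, and the slope is the only dedicated calibration statistic named for internal validation.

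**3. Illustrative size.** The article gives neither the conditional trend nor the entry-date distribution, so both are assumed. Set risk at the start to 1 and let it change linearly to R at the end. The pooled mean is (1 + R)/2 for uniform entry, and 0.5 + 0.5 × (1 + R)/2 if half enter at the start and the rest uniformly. O/E for the latest entrants is R divided by that mean.

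| R | Uniform entry | Half at start | All at start |
|---|---|---|---|
| 0.90 | 0.90/0.95 = 0.95 | 0.90/0.975 = 0.92 | 0.90 |
| 1.00 | 1.00 | 1.00 | 1.00 |
| 1.10 | 1.10/1.05 = 1.05 | 1.10/1.025 = 1.07 | 1.10 |
| 1.20 | 1.20/1.10 = 1.09 | 1.20/1.05 = 1.14 | 1.20 |
| 1.36 | 1.36/1.18 = 1.15 | 1.36/1.09 = 1.25 | 1.36 |
| 1.72 | 1.72/1.36 = 1.26 | 1.72/1.18 = 1.46 | 1.72 |

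R = 1.72 attributes the entire rise in case numbers to conditional risk.

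A log-linear projection to 2019 gives a similar picture. With annual log drift ln(1.72)/20 = 0.0271, O/E = exp[f × 0.0271 × (2019 − c)], where f is the share of the rise that is conditional and c the year on which entries centre:

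| f | c = 1998 | c = 2003 | c = 2008 |
|---|---|---|---|
| 1 | 1.77 | 1.54 | 1.35 |
| 0.5 | 1.33 | 1.24 | 1.16 |
| 0.25 | 1.15 | 1.11 | 1.08 |

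**4. Country and era side by side.**

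| | CPRD-GOLD | CHS |
|---|---|---|
| Country | UK | Israel |
| Index dates | 1998–2018 | 1 January 2019 |
| Diagnosis coding | Read, with ICD-10 for linked hospital and death data | ICD-9 |
| Ethnicity | recorded, or unrecorded category | population sector and socioeconomic score |

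There is one dataset per country and no overlap in index dates, so the contrast between them cannot be divided into country and era.

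**5. Precision of a check by period.** About 2 million patients × 20% = 400 000 in the test set, before age and prior-AF exclusions. The CHS 6-month risk is 4330/2 159 663 = 0.20%. Assuming it applies in CPRD, about 802 events are expected. With a 95% margin on log O/E of 1.96/√events:

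- a period holding a quarter of entries: about 200 events, 1.96/√200 = 0.14, roughly ±14%;
- a period holding a tenth: about 80 events, 1.96/√80 = 0.22, roughly ±22%.

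Under these assumptions, large drift would be visible and drift of a few per cent would not.

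**The case against.** The strongest reply is that the Introduction's trend does not measure drift. It counts new cases. Population growth drops out of an individual risk model, and ageing and comorbidity are at least partly absorbed because age and recorded diseases are predictors. Nor is the direction fixed. An absent code is read as absent disease, so if recording became more complete, later patients would carry more codes and predictions could move upward; the article reports rising completeness only for ethnicity. All of this stands. A reader might infer that the model will under-predict for today's patients by half or more; the document does not support that.

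A reader might also infer that calibration in recent data is untested altogether. It is not: CHS is recent, and calibration plots, Brier score and clinical utility are planned there. What is missing is recent UK calibration.

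It can further be said that CHS differs in coding and ethnicity surrogates too, so a UK result by period would not isolate country. That is right, but it would inform the era component, which nothing planned does.

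A temporal hold-out of, say, 2014–2018 entries may look the natural remedy. It would damage Aim 2: the test set also supplies the cumulative incidences at 5 and 10 years, data end on 30 November 2018, and nobody entering from January 2014 would reach 5 years of follow-up. It would also remove the newest data from training.

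Finally, a random split is a conventional choice, and supplementary stratification is often left to a fuller plan. But the split, the subgroup list and the geographical reading of CHS are all stated here, and together they leave Aim 3 open to misreading.

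**Conclusion.** The point holds in limited form. Internal calibration, as set out, cannot reveal calendar drift, and a calibration shortfall in CHS could not be attributed to geography rather than to calendar time. Both follow from the stated index dates, split, subgroups and validation cohort, without any assumption about the size of drift.

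The size itself is unknown. The illustrative O/E values above 1 run from about 1.05 to about 1.8, depending on how much of the rise in case numbers is assigned to conditional risk and on when patients entered. They are not forecasts, and values at or below 1 are not excluded. The consequence is confined mainly to absolute-risk outputs. This is not a fatal flaw, but it should be addressed before the model is locked, because it changes what Aim 3 can conclude.

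**What to change.** - Keep the random 80:20 split, since the test set is needed for the 5- and 10-year analyses.
- Add period of entry to the performance subgroups under Internal validation, for example 1998–2003, 2004–2008, 2009–2013 and 2014–2018. Report O/E (or calibration intercept), calibration slope and AUROC with confidence intervals in each.
- Under External validation, state that CHS calibration will be read against the latest CPRD period as well as the pooled result, and that the comparison combines country, coding and any remaining difference in era.
- If drift is seen, report a recalibrated version beside the unadjusted one: an intercept update for logistic regression and a separate recalibration layer for the random forest. Estimate it on recent training entries and fix it before the model goes to CHS.

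The cost is one more subgroup table from entry dates already held, with wider intervals in the latest period. Training and test sets are unchanged, and the sample size figure is unaffected.

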#### Internal validation

We will evaluate the model performance using a validation cohort with internal bootstrap validation with 200 samples. The model will be applied to the testing dataset with the same predictor variables. The area under the receiver operating characteristic curve (AUROC) will be used to evaluate predictive ability (concordance index) with 95% CIs calculated using the DeLong method.^38^ Youden’s index will be established for the outcome measure as a method of empirically identifying the optimal dichotomous cut-off to assess sensitivity, specificity, positive predictive value and negative predictive value. We will calculate the Brier score, a measure of both discrimination and calibration, by taking the mean squared difference between predicted probabilities and the observed outcome. To assess the clinical impact of using prediction model as opposed to other risk prediction scores, we will calculate the case reclassification, non-case reclassification and overall net reclassification index at the risk threshold that equates to the average 6 months incidence rate in the cohort and conduct a decision curve analysis, which assesses across threshold probabilities whether the predictive model would do more benefit than harm. Calibration will be assessed graphically by plotting predicted AF risk against observed AF incidence and quantified using a calibration slope.

The same methods will be employed in subgroups by age (<65 years, ≥65 years, <75 years, ≥75 years), sex (women, men) and ethnicity (white, black, Asian, others and unspecified) to assess the model’s predictive performance across clinically relevant groups.

The performance of the prediction model will be compared with the CHA_2_DS_2_-VASc and C_2_HEST scores. The CHA_2_DS_2_-VASc score was originally developed to predict stroke risk in individuals with AF, and the C_2_HEST score for Asian people without structural heart disease.^19^ These algorithms are robust to missing data in routinely collected primary care EHRs and have been tested for AF risk prediction in European cohorts.^19^ Other algorithms that can only be applied to a minority of European primary care EHRs (Pfizer-AI, CHARGE-AF) will not be considered as they cannot be implemented at scale to inform AF screening.^17 27^

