Several randomised clinical trials (RCTs) have shown that serial or continuous non-invasive ECG monitoring in older people with stroke risk factors/elevated N-terminal pro B-type natriuretic peptide, leads to a higher detection rate of previously undiagnosed AF compared with routine standard of care, though yields remain relatively low (3.0%–4.4%).^11–14^ The STROKESTOP (Systematic ECG Screening for Atrial Fibrillation Among 75 Year Old Subjects in the Region of Stockholm and Halland, Sweden) RCT, where AF screening was offered to individuals aged 75 and 76 years without exclusions, achieved only a 3% yield of new AF cases with a modest benefit in a composite outcome of ischaemic or haemorrhagic stroke, systemic embolism, bleeding leading to hospitalisation and all-cause death; and not for each of ischaemic stroke, haemorrhagic stroke or hospitalisation for major bleeding.^15^ Accordingly, for AF screening to be effective the yield of newly diagnosed AF among participants needs to be improved and the intervention offered may have to extend beyond only oral anticoagulation for stroke prophylaxis (figure 1).

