#### Quantification of the association between short-term predicted AF risk and long-term AF and other diseases

We will include all patients randomly assigned to the testing dataset in CPRD-GOLD by the Mersenne twister pseudorandom number generator, categorised as lower or higher predicted AF risk by the developed prediction model at baseline (point of entry to the study). For long-term AF risk, we will plot Kaplan-Meier plots for individuals identified as higher and lower predicted risk of AF to assess the event rate for AF censored at 10 years, and calculate the hazard ratio (HR) for AF between higher and lower predicted risk of AF using the Cox proportional hazard model with adjustment for the competing risk of death. This will inform us of whether short-term AF risk is also associated with long-term AF risk, and whether an individual who undergoes risk-guided AF screening should be considered for repeated AF screening at a later time point (eg, 1 or 5 years).

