#### External validation

The CHS dataset will then be used to externally validate the model performance to assess transportability. A lack of external validation hampers the implementation of prediction models in routine clinical practice.^41^ The prediction model will be saved, including the RF structure, predictor variables and outcome variable into a standalone file. The file will be passed onto the external international collaborators so that they can apply the model to their local external cohort to generate predicted probability of experiencing AF at 6 months for each patient. Then the predicted probability will be compared against the observed outcome in the external cohort to assess the performance of the model. Prediction performance will be quantified by calculating the AUROC, Brier score and by using calibration plots, and the same aforementioned clinical utility and subgroup analysis will be conducted. The performance of the prediction model will be compared with the CHA_2_DS_2_-VASc and C_2_HEST scores.

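### As written, the Youden cut-off is chosen in the test data and re-chosen in each subgroup, so subgroup accuracy is not comparable; one cut-off should be fixed in the training data

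*Protocol article*

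**What the plan says.** All references are to the protocol article.

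- **Prediction model development.** CPRD-GOLD is split 80:20 at random. Grid search and 10-fold cross-validation in the training part tune model parameters. No cut-off is mentioned there.
- **Internal validation.** A bootstrap with 200 samples is named. Then: "The model will be applied to the testing dataset with the same predictor variables". Two sentences later, Youden's index is introduced as "a method of empirically identifying the optimal dichotomous cut-off to assess sensitivity, specificity, positive predictive value and negative predictive value". The data set from which the cut-off comes is not named separately.
- **Internal validation, subgroups.** "The same methods will be employed in subgroups by age", and likewise by sex and by five ethnicity categories.
- **Internal validation, other thresholds.** Net reclassification uses a different threshold, the mean six-month incidence. Decision curves run across thresholds.
- **External validation.** The file passed to CHS is described as including the forest, its predictors and the outcome; no cut-off is listed. AUROC, Brier score and calibration plots are named for CHS, and "the same aforementioned clinical utility and subgroup analysis will be conducted".
- **Quantification of the association between short-term predicted AF risk and long-term AF and other diseases.** The same testing patients are "categorised as lower or higher predicted AF risk by the developed prediction model at baseline".

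**The concern.** Sensitivity, specificity and predictive values belong to a rule: this model at this cut-off. If the cut-off is the one that maximises sensitivity plus specificity in the data at hand, two things follow.

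First, the figures are somewhat too good, because the same outcomes choose the cut-off and score it. The fewer the events, the larger this effect.

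Second, and more important here, each subgroup gets its own rule. Subgroup analysis is meant to show whether one rule that a practice could use works as well in, say, people under 65 as in those 75 and over. Age is itself a predictor, so predicted risks will differ between these groups. A cut-off that moves with the subgroup absorbs that difference, and the table would not show that a common cut-off misses most cases in one group or flags most people in another.

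The article states its selection rule. The point is therefore about how that rule works, not about detail that a condensed article may leave out.

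**Working it through.** **The plan's own figures.** The article gives no value for the cut-off or its accuracy, so there is nothing to reproduce on this point. Its one computed sample size does reproduce: 200 / [(0.95 - 1) x ln(1 - 0.01/0.95)] = 377,996. It does not bear on the cut-off.

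**Step 1. Events in the test set.**
- CPRD size: about 2 million (Data sources and permissions); 20% is about 400,000.
- CHS six-month risk: 4330 / 2,159,663 = 0.2005% (same section).
- Assuming that risk for CPRD: 400,000 x 0.2005% = about 800 events.
- Rough check: 200,000 AF records among 2 million is 10% over about 42 half-years, or about 0.24% per half-year if the records are incident. That gives about 960 events, the same order.
- Range examined: about 150 events (377,996 x 20% x 0.2005% = 152) to 6800 (400,000 x 1.7%, the article's prevalence figure).

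**Step 2. Comparability.** Assume normal scores with equal variance (SD 1) in cases and non-cases, and AUROC 0.80 in every group.
- Separation d = sqrt(2) x Phi^-1(0.80) = 1.190; the Youden cut-off lies at d/2 = 0.595 above the non-case mean.
- If a subgroup's scores shift by s, a re-chosen cut-off moves with it: sensitivity = specificity = Phi(0.595) = 0.724 for any s.
- A fixed cut-off gives specificity Phi(0.595 - s) and sensitivity Phi(0.595 + s).

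| Shift s (SD) | Fixed: sensitivity / specificity | Re-chosen: sensitivity / specificity |
|---|---|---|
| -1 | 0.34 / 0.94 | 0.72 / 0.72 |
| -0.5 | 0.54 / 0.86 | 0.72 / 0.72 |
| 0 | 0.72 / 0.72 | 0.72 / 0.72 |
| +0.5 | 0.86 / 0.54 | 0.72 / 0.72 |
| +1 | 0.94 / 0.34 | 0.72 / 0.72 |

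**Step 3. Optimism.** Under the same score model, the Youden cut-off was chosen in a simulated sample. The apparent J (sensitivity + specificity - 1) was compared with the true J of that same cut-off. There were 1000 replicates for 20 to 150 events, 400 for 800 and 100 for 6800. Non-cases were set by the 0.2005% incidence and capped at 200,000.

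| Events in the sample used | Mean optimism in J, AUROC 0.75 to 0.85 |
|---|---|
| 6800 | 0.002 to 0.003 |
| 800 | 0.007 to 0.011 |
| 150 | 0.025 to 0.029 |
| 50 | 0.054 to 0.062 |
| 20 | 0.090 to 0.101 |

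Nearly all of it falls on sensitivity. The cut-off itself is also imprecise: with 800 events and AUROC 0.80, the true sensitivity at the chosen cut-off has a 95% range of 0.64 to 0.79.

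**The case against.** **Same-data selection is inferred from the order of sentences, and the 200-sample bootstrap might correct it.** It is an inference, but the natural one: the model has just been applied to the testing data, and tuning in training covers model parameters only. The bootstrap would remove the optimism only if the cut-off were re-selected in every sample, which is not stated. It would not make subgroups comparable in any case.

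**The overall harm is negligible.** This stands for the whole test set. A reader might infer that the headline accuracy will be materially inflated; at about 800 events the figure is about 0.01 in J. The larger values need 20 to 50 events, and the article gives no event counts for any subgroup. Age and sex groups need not be sparse.

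**CHS.** A reader might infer that the cut-off will be re-chosen in CHS, or that no decision threshold is ever validated externally. The text supports neither. External validation does not name Youden's index or sensitivity and specificity; they could enter only through the subgroup wording. Clinical utility there most naturally means net reclassification and decision curves, which do assess thresholds in CHS. The description of the transferred file is not exhaustive. What stands is that no fixed Youden cut-off is shown as carried over.

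**Youden weights sensitivity and specificity equally, which may suit screening poorly.** The article does say of earlier trials "though yields remain relatively low", but those yields come from ECG monitoring of older people and are no benchmark for coded six-month incidence in adults over 30. Decision curves already cover other weightings. This is a preference, not a fault in the plan.

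**Conclusion.** The point holds, limited to the Youden cut-off. As written, the cut-off is selected and assessed in the same testing data and re-selected in each age, sex and ethnicity subgroup, and none is listed for transfer to CHS.

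The main consequence is that subgroup sensitivity, specificity and predictive values would refer to different rules. With scores shifted by half an SD, a table of about 0.72/0.72 could stand where a common rule gives 0.54/0.86 or 0.86/0.54. Optimism is secondary: about 0.01 in J overall, and about 0.05 to 0.10 in any subgroup with 20 to 50 events.

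These sizes rest on assumptions that the article does not supply: AUROC (0.80 for comparability, 0.75 to 0.85 for optimism), normal scores of equal variance, the CHS incidence applied to CPRD, and the subgroup shifts and event counts. The loss of comparability does not depend on their exact values. AUROC, Brier score, calibration and decision curves are unaffected.

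**What to change.** Choose one cut-off by Youden's index from the cross-validated predictions in the 80% training data, and lock it in the file with the model. Report sensitivity, specificity, PPV and NPV at that value, unchanged, in the test set, in every subgroup and in CHS. State that the same cut-off defines higher and lower predicted risk for the long-term AF and non-AF analyses.

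The cost is a few sentences of protocol text and minor code. Overall accuracy figures will be slightly less favourable, and subgroup figures may look less uniform, which is the information sought. Reporting accuracy at fixed fractions of highest predicted risk is an optional addition.
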